### 5.5.5. CYP isoform-selective substrates

In vitro data indicate that regorafenib is a competitive inhibitor of the cytochromes CYP2C8 (Ki value of 0.6 micromolar), CYP2C9 (Ki value of 4.7 micromolar), and CYP2B6 (Ki value of 5.2 micromolar) at concentrations that are achieved in vivo at steady state (peak plasma concentration of 8.1 micromolar). The in vitro inhibitory potency towards CYP3A4 (Ki value of 11.1 micromolar) and CYP2C19 (Ki value of 16.4 micromolar) was less pronounced.

A clinical probe substrate study was performed to evaluate the effect of 14 days of dosing with 160 mg regorafenib on the pharmacokinetics of probe substrates of CYP2C8 (rosiglitazone) CYP2C9 (S-warfarin), CYP 2C19 (omeprazole) and CYP3A4 (midazolam).

Pharmacokinetic data indicate that regorafenib may be given concomitantly with substrates of CYP2C8, CYP2C9, CYP3A4, and CYP2C19 without a clinically meaningful drug interaction.

### 5.5.6. Antibiotics

The concentration-time profile indicates that regorafenib and its metabolites may undergo enterohepatic circulation. Co-administration of antibiotics that affect the flora of the gastrointestinal tract may interfere with the enterohepatic circulation of regorafenib and may result in a decreased regorafenib exposure. The clinical significance of these potential interactions is unknown, but may result in a decreased efficacy of regorafenib.

### 5.5.7. Bile salt-sequestering agents

The concentration-time profile indicates that regorafenib and its metabolites may undergo enterohepatic circulation. These compounds may interact with regorafenib by forming insoluble complexes which may impact absorption (or reabsorption), thus resulting in potentially decreased exposure. The clinical significance of these potential interactions is unknown, but may result in a decreased efficacy of regorafenib.

### 5.5.8. Permissible concomitant medications and treatments

- Standard therapies for concurrent medical conditions. Prophylactic anti-emetics may be administered according to standard practice.
- Treatment with non-conventional therapies (eg, herbs or acupuncture) or vitamin/mineral supplements is acceptable provided that such agents do not interfere, in the opinion of the investigator, with the study endpoints.
- Bisphosphonates
- Clinical data indicate that regorafenib has no effect on digoxin pharmacokinetics, therefore can be given concomitantly with p-glycoprotein substrates, such as digoxin, without a clinically meaningful drug interaction.
- Subjects taking narrow therapeutic index medications, such as warfarin, quinidine and cyclosporine, should be monitored proactively. A subject treated with warfarin or heparin will be allowed to participate provided that the anticoagulant dose and PT-INR and aPTT values are stable. Close monitoring (evaluation  $\geq$  once weekly) is recommended. If either value is above the therapeutic range, the anti-coagulant dose should be modified and the assessments should be repeated once weekly until the value is stable.
- Contrast agents used in CT or MRI scans (these do not need to be entered in the Concomitant Medications CRF).
- G-CSF and other hematopoietic growth factors may be used during the study for the management of acute toxicity such as febrile neutropenia when clinically indicated or at the discretion of the investigator; however, they may not be substituted for a required dose reduction. Long-term administration of erythropoietin is permitted.

### 5.5.9. Prohibited concomitant medications and treatments

- Systemic anti-cancer therapy including cytotoxic therapy, signal transduction inhibitors, immunotherapy, and hormonal therapy
- Tyrosine kinase inhibitors
- Bone marrow transplant or stem cell rescue
- Use of biologic response modifiers, such as G-CSF within 3 weeks of study entry
- All traditional medicines with an anti-cancer indication, including traditional Chinese medicine (Appendix 22.3)
- St. John's Wort
- Grapefruit or grapefruit juice

Following dose modification of the study drug, therapeutic monitoring of concomitant medications should be performed as needed in a manner consistent with the local clinical standard of care. In general, subjects should be closely monitored for side effects of all concomitant medications regardless of the path of elimination.

## 6. STUDY PROCEDURES

### 6.1 Screening visits/procedures

Screening procedures may be completed during multiple visits but must be completed within the specified timeframes before the first dose of study drug.

***Screening procedures to be completed or that must be available within 28 days prior to initiation of study treatment:***

- Obtain written ICF. No screening procedures may be performed until written informed consent has been obtained.
- Demographics
- Medical history including allergies and prior conditions
- Histologically confirmed diagnosis of colorectal adenocarcinoma
- Tumor assessment: CT or MRI eligibility scan (chest, abdomen, pelvis, and other suspected sites as applicable) meeting the standard of care for the imaging of the respective organ system(s).
- 12-lead ECG
- Review inclusion/exclusion criteria

***Screening procedures to be completed within 14 days prior to initiation of study treatment:***

- 18FDG-PET CT scan

**Screening procedures to be completed within 7 days prior to initiation of study treatment:**

- ECOG performance status
- Physical examination
- Documentation of AEs (CTCAE v 4.0 grading)
- Record all concomitant prescribed and over-the-counter medications (including start/stop dates, dose, and indication). All medications and significant non-drug therapies taken within 14 days prior to the start of study drug should be entered in the eCRF; all concomitant medications taken from this visit until 30 days after the last dose of study drug should be recorded at each study visit.
- Perform the following laboratory evaluations:
  - CBC with differential. Specified platelet count ( $\geq 100,000$  cells/mm^3), hemoglobin concentration ( $\geq 9$  g/dL), and ANC ( $\geq 1500$  cells/mm^3) must be met *without* transfusion, or G-CSF and other hematopoietic growth factors
  - Chemistry and electrolyte panels
  - A pregnancy test for women of childbearing potential; a negative result is required before initiating study treatment. More frequent evaluation for pregnancy may be required in certain countries; all local regulations regarding pregnancy testing in clinical study subjects must be followed.
  - A urinalysis by dipstick, and a microscopic analysis if the urine dipstick test shows a change from normal
  - Proteinuria qualification
  - GFR calculation
  - Coagulation panel. Subjects treated with warfarin or heparin will be allowed to participate in the study if no underlying abnormality in coagulation parameters exists per prior history; weekly evaluation of PT-INR/aPTT will be required until stability is achieved (as defined by local standard of care and based on prestudy PT-INR/aPTT values).
- CEC and CEP counts (results will not be communicated to the patient and the treating physician)
- Blood samples to be stored for evaluation of cytokines, circulating angiogenic factors, cfDNA mutations and miRNA plasma levels as well as for pharmacogenetic studies.

## 6.2 Treatment visits/procedures

See Section Schedule of procedures/assessments.

Each treatment cycle comprises 4 weeks. Regorafenib will be administered on a 3-weeks-on/1-week-off dosing schedule.

During Cycles 1 and 2, study visits will be scheduled on Days 1, 8, 15, and 22 and on Day 1 of each cycle from cycle 3 onwards. From Cycle 3 to the end of treatment, visits on Day 15 may be scheduled at the discretion of the investigator; if scheduled, visits on Day 15 should include the same procedures as were performed on Day 15, Cycle 2 (except for the plasma biomarker sampling).

ALT, AST, and bilirubin must be obtained at baseline and monitored weekly during the first two cycles of treatment with regorafenib (ie, on Days 1, 8, 15, and 22 of Cycles 1 and 2 [ $\pm 3$  days]), even if values are normal. The investigators may use investigational site or local laboratory AST, ALT, or bilirubin values; these values must be entered in the eCRF.

Blood pressure monitoring is required to be completed weekly for the first 6 weeks of treatment.

GFR calculations must be done within 7 days of study start, then on Day 1 for the first 6 cycles, and at EOT. Additional calculations may be done at the discretion of the investigator.

CEC and CEP counts, blood samples to be stored for evaluation of cytokines, circulating angiogenic factors, cfDNA mutations and miRNA plasma levels will be performed on day 14th  $\pm 2$  after starting treatment, before starting the 2nd cycle (day 28) at the first restaging (after 6 weeks) and at progression of the disease

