### 5.3. Definitive interruption of study treatment

A subject can definitively interrupt study treatment for the following reasons:

- Unequivocal progression of disease as demonstrated on a CT/MRI scan. In the case of equivocal lesions, subjects should continue to receive study drug until progression is confirmed (CT/MRI scan, follow-up).
- If, in the investigator's opinion, continuation in the study would be harmful to the subject's well-being
- At his/her own request or at the request of his/her legally acceptable representative. At any time during study treatment and without giving a reason, a subject or his/her legally acceptable representative may decline further study treatment. The subject will not suffer any disadvantage as a result. The subject will continue to be followed up for safety and survival unless he/she withdraws consent.
- Study drug dose reduction by more than two dose levels
- Study drug dose interruption for more than one cycle (4 consecutive weeks; maximum of 5 weeks between doses of regorafenib)
- Severe allergic reactions, such as exfoliate erythroderma, anaphylaxis, or vascular collapse
- Any other adverse reaction deemed sufficiently serious to warrant discontinuation of treatment by the investigator
- If female, a pregnancy test result consistent with pregnancy
- Use of illicit drugs or other substances that may, in the opinion of the investigator, have a reasonable chance of contributing to toxicity or otherwise confounding the results of the study
- Development of any intercurrent illness or situation that may, in the judgment of the investigator affect assessments of clinical status and study endpoints to a relevant degree
- Development of a second malignancy except for cervical cancer in situ, nonmelanoma skin cancer, or superficial bladder tumors classified as noninvasive tumor (Ta), carcinoma in situ (Tis), or tumor invades lamina propria (T1).
- Any subject who definitively interrupt study treatment will be evaluated at the End-of-treatment Visit conducted 30 days ( $\pm 7$  days) after permanently stopping study treatment.
- In all cases, the reason for definitive interruption of study treatment must be entered in the electronic Case Report Form (eCRF) and in the subject's medical records.

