### 6.3 End-of-treatment visit

The End-of-Treatment assessments should be performed no later than 14 days after study treatment has stopped.

- Determination of disease status: see paragraph 7 (*Response Evaluation*)
- 12-lead ECG
- Documentation of AEs (CTCAE v 4.0 grading)
- Concomitant medications
- ECOG performance status
- Physical examination, including BP measurement
- The following laboratory evaluations will be performed
  - CBC with differential
  - Chemistry and electrolyte panels

- A coagulation panel, including PT-INR and aPTT
- GFR calculation
- AST, ALT, and bilirubin
- Perform drug accountability

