| CBC with differential i                                           |                                             |                | X       | X f       |       | X              |        | X                    |       | X              |        | X                         |
| Chemistry / electrolyte panel                                                |                                             |                | X       | X f       |       | X              |        | X                    |       | X              |        | X                         |
| Blood for CEC and CEP counts j                                    |                                             |                | X       |                      |       | X              |        | X                    |       |                |        |                           |
| Blood for biomarkers                                                         |                                             |                | X       |                      |       | X              |        | X                    |       |                |        |                           |
| Pregnancy test k                                                  |                                             |                | X       |                      |       |                |        |                      |       |                |        |                           |
| Urinalysis by dipstick (with microscopic analysis if indicated) l |                                             |                | X       | X f       |       | X              |        | X                    |       | X              |        | X                         |
| Proteinuria quantification (if indicated) l                       |                                             |                | X       | X f       |       | X              |        | X                    |       | X              |        | X                         |
| GFR calculation m                                                 |                                             |                | X       | X f       |       |                |        | X                    |       |                |        | X                         |

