| Coagulation panel n                                               |                                             |                | X       | X f       |       | X o |        | X                    |       | X n |        | X                         |

|                                        |  |   |   |   |   |   |   |   |   |   |   |
|----------------------------------------|--|---|---|---|---|---|---|---|---|---|---|
| AST, ALT, bilirubin p       |  | X | X | X | X | X | X | X | X | X |   |
| Blood pressure monitoring q |  | X | X | X | X | X | X | X | X |   | X |
| Drug dispensing                        |  |   | X |   |   |   | X |   |   |   | X |
| Drug accountability                    |  |   |   |   |   |   | X |   |   |   | X |

| Treatment Phase                           | End-of-treatment | Safety Follow-up r      | Survival Follow-up s |
|-------------------------------------------|------------------|------------------------------------|---------------------------------|
| Days                                      |                  | 30 ( $\pm$ 7) days after last dose | Q3 months                       |
| CT/MRI scan d                  | X                |                                    |                                 |
| 12-lead ECGg                              | X                |                                    |                                 |
| AEs and toxicities h           | X                | X                                  |                                 |
| Concomitant medications                   | X                | X                                  |                                 |
| ECOG performance status                   | X                |                                    |                                 |
| Physical examination                      | x                |                                    |                                 |
| CBC with differential                     | X                | X                                  |                                 |
| Chemistry / electrolyte panel             | X                | X                                  |                                 |
| Blood for CEC and CEP counts j | X                |                                    |                                 |

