## 10. BIOMARKERS

### 10.1. Blood sample collection and analysis

Peripheral blood samples will be collected in EDTA tubes through 21G needles and stored as described below:

- at baseline (BL) (4 tubes)
- at day 14 of cycle 1 (C1) (2 tubes)
- at day 28 of cycle 1 (C2) (2 tubes)
- at the first restaging (R) (4 tubes)
- at progression of disease (PD) (4 tubes).

The following tests will be performed on blood samples but, given their uncertain values, these results will not be communicated to the patients and the treating physician:

- **Analysis of polymorphisms** in VEGF, VEGFR, CYP3A4 and UTG1A9 genes (at baseline only).  
Peripheral blood will be collected at BL in EDTA tubes through 21G needles, aliquoted and stored at -80°C. DNA from will be obtained using the DNA extraction kit (Qiagen/SABiosciences) following manufacturer instructions. The expression of the indicated polymorphisms will be evaluated by using pyrosequencing technology with specific 5'-biotinylated primers. Sequencing primers will be developed using SNP Primer Design software from Biotage. Genotyping will be done using a PyroMark ID pyrosequencer according to the manufacturer's instructions. Polymorphisms of these genes may affect activity and toxicity of treatment. One peripheral blood sample for each patient is adequate.
- **Analysis of CECs and CEPs** (at each of the above reported time-points).  
Peripheral blood will be collected, at all the time points previously described, in EDTA tubes through 21G needles and cell suspensions will be evaluated, after red cell lyses. Analysis of CEC/CEP should be performed within 24 h from collection of sample stored at 4 °C by flow cytometry. CECs are defined as negative for haematopoietic marker CD45, positive for endothelial markers P1H12. CEPs are defined as negative for haematopoietic marker CD45, positive for endothelial markers VEGF-R2 and positive for progenitor marker CD34. Vitality will be evaluated by staining with Syto 16.
- **Analysis of circulating angiogenic factors and cytokines** (at each of the above reported time-points).  
Peripheral blood will be collected in EDTA tubes through 21G needles aliquoted and stored at -80°C. The analysis will be done with the Bio-Plex™ technology.
- **Analysis of cfDNA mutations** (at each of the above reported time-points).  

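### The Table 6 grid disagrees with Sections 6.2 and 10.1 and with its own notes on the week-6 and progression blood draws, and the end-of-treatment visit has two dates

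*Protocol*

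**What the plan says.** **Text sections.** Section 10.1 lists five collection times: baseline, day 14, day 28, first restaging and progression. The last two appear as "at the first restaging (R) (4 tubes" and "at progression of disease (PD) (4 tubes", four tubes each. Section 6.2 gives the four post-baseline times, ending "at the first restaging (after 6 weeks) and at progression of the disease", and covers CEC/CEP, cytokines, angiogenic factors, cfDNA and miRNA.

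**Table 6, treatment part.** The rows "Blood for CEC and CEP counts" and "Blood for biomarkers" are both marked at screening (day -7), cycle 1 day 15 and cycle 2 day 1, and nowhere else. The CEC/CEP row carries note j. The biomarker row carries no note letter.

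**Table 6, end-of-treatment part.** There is a CEC/CEP row, again with note j, and no row for stored biomarker blood.

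**Table 6 notes.** Note j names the first restaging and progression for CEC/CEP, cytokines, angiogenic factors and miRNA. It leaves out cfDNA. Note 1, like Section 6.2, exempts optional day-15 visits from cycle 3 onwards from the plasma biomarker sampling done at cycle 2 day 15.

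**End-of-treatment visit.** Section 6.3 states: "The End-of-Treatment assessments should be performed no later than 14 days after study treatment has stopped". Its list of assessments contains neither blood draw. Section 5.3 says that a patient who stops "will be evaluated at the End-of-treatment Visit conducted 30 days" (±7) after stopping. Table 6 has an end-of-treatment column and a separate safety follow-up column at 30 ±7 days.

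**The concern.** A visit schedule is what site staff commonly work from day to day. Here the grid, its notes, the visit list and the text sections do not describe the same set of draws.

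The secondary aims include the prognostic and predictive value of CEC/CEP at baseline and during treatment, and Section 10.2 plans comparisons of biomarker levels before and after treatment. With at most 46 evaluable patients, each missed sample counts. A missed CEC/CEP sample cannot be made good later, because Section 10.1 requires the analysis within 24 hours of collection.

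The late sample has a further problem. The text and note j define it by progression, but the grid marks it only at end of treatment. These are different events for some patients. Section 9.1 expressly provides for patients who stop regorafenib for drug-related adverse events, start no other antineoplastic treatment, and are followed until progression.

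**Working it through.** The plan states no figure to reproduce. The check sets the places side by side.

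| Time point | Sections 6.1, 6.2, 10.1 | Grid: CEC/CEP row | Grid: biomarker row | Note j |
|---|---|---|---|---|
| Baseline | required | marked, day -7 | marked, day -7 | not covered |
| Day 14 | required | marked, C1D15 | marked, C1D15 | named, no cfDNA |
| Day 28 | required | marked, C2D1 | marked, C2D1 | named, no cfDNA |
| First restaging, week 6 | required | blank | blank | named, no cfDNA |
| Progression | required | marked at end of treatment | no row | named, no cfDNA |

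**Where week 6 falls.** Week 6 is day 6 × 7 = 42. Cycles last 28 days, and 42 − 28 = 14, so week 6 is cycle 2 day 14, matching the cycle 2 day 15 column. The restaging CT is marked in that column and both blood rows are blank. Note 1 and Section 6.2 presuppose plasma sampling at that same visit, so the grid contradicts its own note.

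**Tubes.** Section 10.1 gives 4 + 2 + 2 + 4 + 4 = 16 tubes per patient. The times at which both rows are marked account for 4 + 2 + 2 = 8. The other 8 belong to the week-6 and progression draws, for which the grid has no mark or only a CEC/CEP mark at end of treatment. This shows how much of the collection depends on reading beyond the grid. It does not estimate a loss.

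**Analytes at the late draw.** Of five groups (CEC/CEP, cytokines, angiogenic factors, cfDNA, miRNA), the grid keeps 1 at end of treatment and note j keeps 4 at progression. Sections 6.2 and 10.1 require all 5.

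**Progression after stopping treatment.** For a patient who stops for toxicity, the end-of-treatment mark comes before progression. The later columns of Table 6, safety follow-up and survival follow-up, have no biomarker blood. The instruction to sample at progression still stands in the text and note j, but no marked visit carries it.

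**Visit dates.** Section 6.3 gives 0 to 14 days after stopping. Section 5.3 gives 30 − 7 = 23 to 30 + 7 = 37 days. The windows do not overlap; their nearest ends are 23 − 14 = 9 days apart. Table 6 and its note r assign 30 ±7 days to the safety follow-up visit, so Section 5.3 disagrees with the table as well as with Section 6.3.

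**The case against.** The strongest reply is that the draws are not absent from Table 6. Note j sits on the CEC/CEP row in both parts and names week 6 and progression for everything except cfDNA. The grid cannot be run from its marks alone in any case: the week-12 and three-monthly CTs exist only in note d. A site that reads the notes and Sections 6.2 and 10.1 would take the samples. This stands, and it rules out the inference, which a reader might draw from the grid, that sites following the schedule will lose these samples. The grid creates a risk and does not establish a loss.

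The cfDNA omission is also softened. Section 10.1 requires cfDNA at every listed time, and its blood is collected and stored in the same way as that for cytokines and miRNA. A site that drew the note j blood might still hold suitable material.

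On the visit dates, Section 5.3 may simply have given the end-of-treatment name to the safety follow-up visit. That is plausible, but the documents do not say so, and the passages still conflict. A reader might go further and infer that the late CEC/CEP sample will often be drawn 23 to 37 days after stopping, or after the next therapy has begun. The table marks CEC/CEP only under end of treatment, and the documents give no figure for when next therapy starts, so this is not supported.

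A reader might also object that day 28 falls in the rest week. All passages agree on that time, and none says the sample must be taken on a dosing day. That is a matter of preference and not an error.

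Note j does not cure three things: the biomarker row has no letter leading to it, no visit is marked for progression after treatment has stopped, and the two visit dates remain.

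**Conclusion.** The schedule contradicts itself and should be corrected. The defects are the unmarked week-6 draw in both rows, the missing stored-blood row in the end-of-treatment part, the silent Section 6.3 list, note j's missing cfDNA and missing link to the biomarker row, a late mark tied to end of treatment where the text says progression, and two end-of-treatment windows that do not overlap.

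The effect is limited. It touches two of the five sampling times, and only at sites that work from the grid or the Section 6.3 list. The documents give no basis for estimating how many sites that would be, so no expected number of lost samples can be stated. Section 10.2 describes the biomarker analyses as hypothesis-generating. The primary endpoint, sample size and stopping rule do not depend on these draws. Correction is still worthwhile because a missed CEC/CEP sample is unrecoverable and the remedy is cheap.

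**What to change.** - In Table 6, mark both blood rows at cycle 2 day 15, and add a stored-blood biomarker row beside CEC/CEP at the late time point.
- Attach note j to both rows and add cfDNA to it.
- State in Table 6 that the late sample is drawn when progression is documented, whether or not the patient is still taking regorafenib.
- Add both draws to the Section 6.3 end-of-treatment list for cases where that visit coincides with progression.
- Reconcile the end-of-treatment visit dates in Sections 5.3 and 6.3 and Table 6, including how that visit relates to the safety follow-up visit.

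The cost is an amendment to one table, one note, one list and the visit timing text. It adds no draw beyond those Sections 6.2 and 10.1 already require.
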